#### Descriptive client data

Descriptive data concern both participants and housing. Here we include data on the prevalence of physical environmental barriers, functional limitations, formal and informal care, living conditions, housing standards, repeated HA, age, gender, country of origin, educational level, employment, and civil status.

At baseline, the HE instrument [48] is used to determine the physical environmental barriers and accessibility problems. HE is a valid and reliable instrument for assessing and analyzing accessibility problems in housing. The instrument is administered in three steps, utilizing a combination of interview and observation: the first step targets the individual by assessing the presence of functional limitations (12 items) and dependence on mobility devices (2 items). The second step assesses the presence or absences of physical environmental barriers in the home and in the immediate outdoor environment (161 items). Finally, based on the assessments in the first two steps, the magnitude of accessibility problems caused by a particular combination of functional limitations, dependence on MDs, and environmental barriers can be calculated using existing algorithms.

In addition, the Montreal Cognitive Assessment (MoCA) is used as a brief cognitive screening tool [49,50]. The MoCA covers a wide range of cognitive functions, such as short-term memory, executive functions, visuospatial abilities, language, attention, concentration, working memory, and temporal and spatial orientation [50].

The first baseline visit, conducted prior to the HA’s implementation, takes approximately 90 minutes. Each of the three visits after the HA (i.e., at 3, 6, and 12 months) takes approximately 45 minutes. This new practice strategy requires that the OT meets each client at least four times in his or her home (T1–T4). The assessment tools used to structure the data collection will differ among these measurement points (see Table 1).

#### Process data

In order to explore and evaluate the process and thus to understand changes in outcomes in the intervention municipalities, multiple methods are used to collect empirical data. The data collection focuses on feasibility, perceptions, and experiences of the intervention by targeting multiple perspectives—namely, those of clients, cohabitants, and OTs. Qualitative, semi-structured interviews with selected participants (i.e., clients and cohabitants) will be conducted before and after the HA in order to gain deeper knowledge about the participants’ expectations and experiences, as well as about the results of the HAs. The interviews will address the following three areas: (1) the intended goal of the HAs; (2) the clients’ and cohabitants’ roles in the decision, how well their needs and desires are met, and how they perceive the communication with various stakeholders; and (3) their long-term experiences and perceptions of the HAs in relation to home and health. The interviews will be audiotaped and conducted by the first author in the participants’ homes.

At the very end of the 5-day training course, the OTs complete an evaluation form focusing on their readiness to apply the new strategy in their daily practice. Facilitation in terms of reflection is an essential part of applying the intervention, and while the individual evaluations, seminars, and focus-group interviews are part of the intervention, the data collected on these occasions are used in the process evaluation, as well. After each assessment occasion, the OTs note whether they have followed the study protocol and in what ways they diverged from it, along with the reason for any non-adherence. Data collected on internal and external drop-outs will also be used to evaluate processes.

### Data analyses

Cross-sectional and longitudinal data analyses will be conducted depending on the research questions and the data, including statistical analyses, health-economic analyses, and qualitative analyses. Qualitative and quantitative data will be sequentially analyzed, and case studies will be developed.

#### Effects on the client level

Statistical analyses will be conducted on the group and sub-group levels, and common descriptive, inferential, and exploratory statistics will be applied. Depending on the characteristics of the variables, parametric and non-parametric statistics will be used, and both variable-based and person-based statistical analysis approaches [51] will be considered. All statistical analyses will be finally decided upon and described in subsequent papers, depending on the specific research questions they target.

Differences between the intervention and control groups in primary and secondary outcomes will be analyzed cross-sectionally at baseline and 3, 6, and 12 months later. Changes over time in outcomes will be calculated by means of a sign test for nominal data, Wilcoxon’s test for ordinal data, and a t-test for interval data. For correlations between single variables, Spearman’s rank correlation will be used, whereas canonical correlations will explore relationships among multivariate combinations of variables [52].

Because the study has a structure in which participants are nested within the municipalities, we will use hierarchical mixed-effects regression models and multi-level modeling approaches to evaluate differences between the intervention and control groups in changes over time in primary outcomes, as measured by the ADL Staircase and UIMH instruments, and in all secondary outcomes. Potential relations between different primary and secondary outcomes will be investigated by means of correlation analyses and Structural Equation Modeling Techniques (SEM). A mixed-linear-effects model will be used to examine the relation between client outcomes and client, as well as environmental characteristics, before and after the HA. The method is a development of regression and ANOVA, allowing a model of “within-subject dependence.” In order to generate knowledge of different groups’ patterns of changes, we will conduct a person-oriented analysis.

Missing data will be imputed following the guidelines for each instrument.

#### Effects on the societal level

Cost, cost-effectiveness, and cost-utility analyses will be performed from the perspective of the municipalities. The analysis of costs will consider the following direct-cost categories in both the experimental and the control groups.

In order to estimate more correctly the resources used in the process of HA, the assistance provided by informal caregivers will also be assessed and considered in the cost analysis. The value assigned to an hour of informal caregivers’ assistance will be equal to the hourly salary of an unskilled care assistant.

The cost-effectiveness analysis will compare the costs and outcomes of the two trial arms. As outcomes measures we will use the ADL dependency change over the trial period and the number of institutionalizations and housing relocations. Because both the costs and the effects of the interventions will occur over a period of one year, it will not be necessary to adjust for the time delay or to discount the measures.

Three incremental cost-effectiveness ratios (ICER) will be calculated by taking the difference in costs divided by the difference in the three outcome benefits between the two groups: one unit of ADL score gain, one institutionalization avoided, one relocation avoided. All available data on client and societal levels will be used to identify the variables included in the analysis in order to answer the hypotheses. The ICER will represent the additional costs of gaining, through the intervention, an additional unit of these outcomes measures.

In a later step, probabilistic sensitivity analyses (PSA) will also be performed on the three models using the software TreeAge Pro 2009. Results from the PSA will be presented as an acceptability curve, graphically illustrating the probability that the intervention is cost-effective over a range of willingness-to-pay values.

A cost-utility analysis (CUA) will estimate the ratio between the cost of an intervention and the benefit it yields in terms of quality-adjusted life years. The PSA of this model will follow a procedure similar to that of the cost-effectiveness analysis.

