### Hypothesis and aims

The hypothesis of this study is that a new intervention strategy for OTs that takes a research-based and structured approach to assessing and evaluating clients who request new HAs can increase the usability of the home; maintain or increase activity, participation, and health-related quality of life, as well as MD use; and decrease fall incidences and the fear of falling (with respect to the standard approach in ordinary practice). An additional hypothesis is that the new intervention strategy will yield health-economic benefits.

The primary aim of this paper is to describe the design of a project evaluating the effects of using a research-based strategy for managing housing adaptations (HAs). The evaluation targets clients’ perspectives in terms of activity, participation, usability, fear of falling, fall incidence, use of mobility devices, and health-related quality of life, and determines the societal effects of HAs in terms of costs. Additional aims of the project are to explore and describe this strategy in relation to experiences and expectations (a) among clients and cohabitants and (b) occupational therapists in ordinary practice.

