The intervention involves conducting structured assessments with standardized measurements. The variables selected are important as outcomes of HA or are included based on the assumption that they contribute to the structure and focus of the OT assessment. Some variables are included for participant-descriptive purposes. The intervention at experimental sites consists of the following structured components:An extensive training course for OTs covering the standardized research-based practice strategy. The 5-day course extends over 3 or 4 weeks. The research project team is responsible for the course and for training the OTs. The course covers how to conduct a structured assessment; how to use comprehensive and validated instruments in a structured way; and the background, purpose, construction, and basic psychometric properties of each study instrument, along with real-life situation assessments. The training also covers procedures for selecting participants and gaining informed consent, and it addresses ethical issues. The training course includes pilot assessments of the OTs before they begin data collection.OT assessments of physical environmental barriers and housing accessibility prior to HA certification.OT assessment of client outcomes in terms of ADL dependence, need for formal and informal help in the home, and MDs prior to HA certification.Client’s self-administered assessments of home usability, fear of falling, retrospective falls, participation and satisfaction, client goal fulfilment, and health-related quality of life prior to HA certification.Follow-up on client outcomes (i.e., according to OT assessments and self-reports) at home visits that take place 3, 6, and 12 months after HA implementation.

To strengthen data validity and reliability and to facilitate the incorporation of the intervention into ordinary practice, the following operations are planned:Project leaders will arrange regular seminars to increase compliance and adherence to the study protocol. The seminars aim to deepen OTs’ understanding of the intervention components and their competence in assessment and data analysis. One seminar in the early phase is organized as a focus-group interview, followed by additional focus-group meetings after 6 and 12 months.Individual contacts with OTs are undertaken via telephone or workplace visits for support and to clarify any questions that arise.

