**Secondary outcome**					
Fear of falling	The Short Falls Efficacy Scale-International [42].	X	X	X	X
Fall incidence	Retrospective self-report on falls incidences during the last six months	X	X	X	X
Mobility devices	Self-reported use and need	X	X	X	X
Participation and satisfaction	Self-reported aspects of participation and satisfaction.	X	X	X	X
Health-related quality of life and quality adjusted life years (QUALYs)	EQ-5D-5L [47].	X	X	X	X
Cost	Item on costs for staff, material, travel, administration, etc.	X	X	X	X
Repeated HA	Self-reported question and register data from the municipality		X	X	X
Relocation	Self-reported question		X	X	X
Formal and informal care	Items on formal and informal care, who, and minutes per week, self-reported	X			X

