Societal levelHealth-economic data are important for societal planning purposes and in this study are collected in the following direct-cost categories: time spent by the OT with each client (both preparation time and direct contact); time other professionals spend with each client; time spent training the OT at the intervention site and other direct costs for training; time and other costs for travel; the cost of other consumables used for each client; the amount of the grant given to each client; and time for the assistance provided by formal and by informal (family) caregivers. Data is collected from an ad hoc resource-use questionnaire compiled by the OTs, by during the follow-up period retrieving grant applications, certificates, invoices and formal grant decisions, related to each case from the municipality office, and by using client-reported data on assistance received by informal caregivers. Data from the EQ-5D-5L instrument can be used for cost-effectiveness calculations, as well.Client relocation data are targeted by using a single dichotomous item question. This outcome is included because relocation to another ordinary or sheltered housing facility is sometimes an alternative to HA or a solution when HA proves insufficient.

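### The economic analysis is declared municipal but includes unpaid family care, and care time is measured only once after the adaptation

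*Protocol article*

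**What the plan says.** **Perspective.** The section on effects on the societal level opens: "Cost, cost-effectiveness, and cost-utility analyses will be performed from the perspective of the municipalities." Its next paragraph says that "the assistance provided by informal caregivers will also be assessed and considered in the cost analysis", with an hour of such help given a value "equal to the hourly salary of an unskilled care assistant". Under Secondary outcomes, societal level, the list of direct-cost categories includes "time for the assistance provided by formal and by informal (family) caregivers", and the informal part is obtained "by using client-reported data on assistance received by informal caregivers". Under Hypothesis and aims, the evaluation "determines the societal effects of HAs in terms of costs".

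**Use of the costs.** The section on effects on the societal level defines three ICERs (per unit of ADL score, per institutionalization avoided, per relocation avoided). Each takes the between-group difference in costs as its numerator. A cost-utility analysis follows. The horizon is one year. No separate municipal-only and societal totals are described.

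**Schedule.** Table 1 describes the care measure as "Items on formal and informal care, who, and minutes per week, self-reported" and marks it at T1 and T4 only. The general cost row, the EQ-5D-5L and the ADL Staircase are marked at all four time points. T1 is before the HA. Follow-up is done "at home visits that take place 3, 6, and 12 months after HA implementation".

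**The concern.** A cost perspective decides whose costs count. A municipal decision-maker who reads a municipal ICER will take its numerator as what the municipality pays. If it also holds imputed wages for unpaid relatives, it answers a different question. A reader who wants the societal answer promised in the aims finds a municipal label on it. The two totals can diverge when care shifts between family and paid staff, and a single total would not show this.

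The schedule raises a separate, smaller issue. Care time is a rate (minutes per week) that must be turned into a 12-month quantity. With one value before the HA and one at 12 months, the data say nothing about the path in between, although visits at 3 and 6 months take place anyway.

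**Working it through.** **1. Perspective, passages side by side.**

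- Declared for all three types of economic analysis: municipal (effects on the societal level, first paragraph).
- Content of the cost analysis: includes informal care at a proxy wage (same section, second paragraph; also the direct-cost list under Secondary outcomes).
- Stated aim: societal (Hypothesis and aims).

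An imputed wage for unpaid family time is no payment by the municipality. The second statement therefore fits the third and conflicts with the first. Because the ICERs are defined from one cost difference, the mismatch carries into all three if informal care is part of that difference, which is the natural reading. The cost-utility analysis falls under the same declared perspective.

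**2. Schedule.** The document gives no care minutes, wages or cost totals, so there is no plan figure to reproduce. What can be checked is how far a 12-month total depends on assumptions. Both arms receive HAs, so the relevant quantity is the between-arm difference in the change in weekly care time. Any change common to both arms cancels.

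Let y(m) be that difference at month m, scaled so that its largest value is 1, with y(0) = 0. The true total is the area under y from 0 to 12. Three ways of computing it are compared:

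- Line from T1 to T4: 12 × (y0 + y12)/2
- T4 rate applied to the whole year: 12 × y12
- Trapezoid on all four visits: 3 × (y0 + y3)/2 + 3 × (y3 + y6)/2 + 6 × (y6 + y12)/2

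The paths are assumptions:

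| Path | True area | T1–T4 line | T4 rate all year | Four visits |
|---|---|---|---|---|
| Step at the HA | 12 | 6 (50%) | 12 (100%) | 10.5 (87.5%) |
| Complete by month 3 | 1.5 + 9 = 10.5 | 6 (57%) | 12 (114%) | 10.5 (100%) |
| Complete by month 6 | 3 + 6 = 9 | 6 (67%) | 12 (133%) | 9 (100%) |
| Linear to month 12 | 6 | 6 (100%) | 12 (200%) | 6 (100%) |
| Peak at month 3, lost by month 12 | 1.5 + 4.5 = 6 | 0 (0%) | 0 (0%) | 6 (100%) |
| None to month 6, then linear | 3 | 6 (200%) | 12 (400%) | 3 (100%) |

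With T1 and T4 alone, the answer depends on both the path and the estimator. Each two-point rule is exact on one of these paths and wrong on the others, in both directions. With four visits the range narrows to 87.5% to 100%. The exact results there arise partly because the bends in these paths fall on visit times, so real data would do somewhat less well.

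**The case against.** The strongest reply has four parts.

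*The inclusion of informal care is open and reasoned.* The protocol says it is there to estimate resource use more correctly, gives the valuation rule, and places it under a societal heading. This is true, and it means the fault lies in the declared perspective rather than in counting the care. It does not make the cost municipal. It is also true that informal care is only said to be considered in the cost analysis. Its entry into each ICER is inferred from the definition and not stated.

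*No interpolation rule is prescribed.* A reader might infer that the plan would capture only half of a care saving, against 87.5% with four visits. The document does not support that. Those figures hold for one path under one estimator. On the same path, applying the T4 rate to the whole year recovers 100%, which is better than four visits. How rates become an annual cost may properly be left to an analysis plan. What the protocol does fix is that only one post-HA value exists.

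*The scale of the effect is unknown.* A reader might set an hour of informal care per week, priced at an assumed wage, against the mean HA cost of EUR 115.5 million / 76,000 = EUR 1,520 from the Background. That is the wrong contrast, because both arms receive HAs and the ICER compares two ways of managing them. Nor can it be said from the document that the sign of the cost difference would change.

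*Most costs are measured more often.* This stands. The sparse schedule affects care time, formal and informal. The general cost row is marked at all four time points, and grants and invoices are retrieved during follow-up. The open-ended wording of that cost row might be read to cover care, but care has its own row and its own schedule.

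**Conclusion.** Two statements hold.

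First, the declared municipal perspective contradicts the inclusion of informal care and does not match the societal aim. As written, the ICERs would bear a label that their content does not fit. This rests on the text alone, with the natural reading that the cost analysis supplies the ICER numerator.

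Second, the care-time part of the one-year cost rests on one post-HA measurement and an assumed path. Under the six illustrative paths, a T1–T4 line recovers 0% to 200% of the true change and the T4 rate 0% to 400%. The error is nil when the path matches the rule. These are shares of the care component only. Their effect on the between-arm cost difference, in size or direction, cannot be derived from the document.

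The first point should be corrected. The second is a worthwhile and cheap improvement. Neither touches the analysis of the primary outcomes.

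**What to change.** **(a) Perspective.** In the section on effects on the societal level, replace the single perspective with two cost totals and two sets of ICERs and cost-utility results from the same data: municipal, with informal care excluded, and societal, with it included. Name the societal set as the one that answers the stated aim. This costs wording and a second run of the same calculation, with no new data. Declaring one consistent perspective would also remove the contradiction, but would lose the comparison that shows any shift between family and paid care.

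**(b) Care time.** Add the existing care items to the T2 and T3 forms, and compute the 12-month care cost from all post-HA measurements, with the rule for the first three months stated in advance. The downside is a few minutes per client at two visits already planned at about 45 minutes each. If those visits have passed, state the rule that turns the T1 and T4 rates into an annual cost, and report how the cost difference and the ICERs change over a set of plausible paths such as those above.

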#### Process exploration and evaluation

To explore the processes behind changes in outcomes on a client and a societal level, quantitative and qualitative data will be analyzed over time.

The qualitative interviews of the clients and cohabitants are exploratory in character and will describe the process of applying for an HA, installing an HA, and using an HA in everyday life. Because the data reflect a process, the analysis will follow the principles of grounded theory according to Charmaz [53].

For each client, HA grant certificates and other documents related to the grant application such as grant proposals, grant decisions and invoices, will be analyzed in order to gain knowledge about the nature of the HA applied for, whether or not HA was granted, and other considerations among the OTs, the grant managers, and the clients and cohabitants.

The type of each HA and formal and informal help will be analyzed quantitatively and combined with survey data and data on drop-out, as well as with qualitative interview data. In addition, quantitative and qualitative data will be combined using mixed-methods analyses [22] in the context of case studies [54].

The process among the OTs will be analyzed by means of the baseline 30-minute paper in which the OTs describe in detail their current HA practices, the evaluation form focusing on their readiness to apply the new practice strategy, and the focus-group interviews. In addition, data about the quality of each OT’s application of the intervention in ordinary practice and on his or her study protocol adherence will be analyzed. For this purpose we will apply descriptive statistics, in combination with conventional and directed content analysis [55].

